#### Follow up images

Once the readers have assessed the baseline scan for a patient (and the case report form has been signed), they read baseline and 6 month images for that patient side-by-side. Based on a subjective evaluation of lesion characteristics at baseline along with lesion changes from baseline to 6 months, the readers will classify individual lesions as malignant or benign. In equivocal or inconsistent cases, baseline and follow-up images from all three imaging modalities will be read and evaluated together. Any new lesions seen on the follow-up scan but not observed on the baseline image on any imaging modalities will not be classified.

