**Methods/Design:**

One hundred forty consecutive, high-risk prostate cancer patients will be recruited from several hospitals in Denmark. Sample size was calculated using Hayen’s method for diagnostic comparative studies. This study will be conducted in accordance with recommendations of standards for reporting diagnostic accuracy studies. Eligibility criteria comprise the following: 1) biopsy-proven prostate cancer, 2) PSA ≥50 ng/ml (equals a prevalence of bone metastasis of ≈ 50 % in the study population on bone scintigraphy), 3) patients must be eligible for androgen deprivation therapy, 4) no current or prior cancer (within the past 5 years), 5) ability to comply with imaging procedures, and 6) patients must not receive any investigational drugs. Planar bone scintigraphy and ^18^F-fluoride positron emission tomography/computed tomography will be performed within a window of 14 days at baseline. All scans will be repeated after 26 weeks of androgen deprivation therapy, and response of individual lesions will be used for diagnostic classification of the lesions on baseline imaging among responding patients. A response is defined as PSA normalisation or ≥80 % reduction compared with baseline levels, testosterone below castration levels, no skeletal related events, and no clinical signs of progression. Images are read by blinded nuclear medicine physicians. The protocol is currently recruiting.

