### Image analysis

Diagnostic accuracy is primarily analysed on a patient-basis. All images are evaluated by a reading committee of two readers who must be board certified in Nuclear Medicine and/or Radiology and experienced with the imaging modality. Readers will have access to PSA, T-stage, Gleason grade, and a standard questionnaire filled out by the patients. The amount of clinical information will be minimised to reduce reading bias but the amount of information will be sufficient to reflect clinical practice and thus, will present the generalisability of the findings. The questionnaire contains information about any artificial joint replacements, prior surgeries to joint or bone, prior skeleton or joint infections, known degenerative or inflammatory bone diseases, recent trauma to the skeleton, and location and duration of any bone pain [8].

All lesions, or a representative sample if a large number of lesions are present, are first classified independently by each reader for malignancy using a dichotomous scale as well as a numerical rating scale which includes an equivocal rating option [30]. The latter scale will be used primarily to determine observer agreement. Eventually, the readers will reach consensus for the dichotomous outcome. If consensus cannot be reached, a third reader will be included and a majority rule will apply. Lesion analysis is then summarised on an individual patient basis. The exact measurement scales and how to handle patients with multiple bone lesions will be stated in a reader manual and the statistical analytical plan (see Data Analysis). Readers may participate in the reading committee for more than one imaging modality.

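### The reading rules let a reader make one modality's baseline call after seeing, on another modality, which of the patient's lesions regressed; no lock across modalities prevents it

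*Protocol article*

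**What the plan says.** - **Protocol article, Follow up images.** Follow-up images become available patient by patient. Readers finish the baseline scan, sign the CRF, and then "they read baseline and 6 month images for that patient side-by-side". From this side-by-side session "the readers will classify individual lesions as malignant or benign". The section adds: "In equivocal or inconsistent cases, baseline and follow-up images from all three imaging modalities will be read and evaluated together".
- **Protocol article, Image analysis.** Reading is organised in committees by modality, and "Readers may participate in the reading committee for more than one imaging modality". No condition on order, interval or separation is attached. On information supplied, "Readers will have access to PSA, T-stage, Gleason grade, and a standard questionnaire filled out by the patients". The section does not say that other modalities' results or follow-up results are withheld at the baseline read.
- **Protocol article, Final diagnosis.** The reference is shared across modalities. A lesion called malignant at baseline counts as a true positive if it responded on the follow-up images of any modality.
- **Protocol article, abstract, Methods/Design.** "Images are read by blinded nuclear medicine physicians". What they are blinded to is not stated.

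**The concern.** The signed CRF protects the baseline read that has just been completed. It does not protect a baseline read of another modality, in the same patient, that the same reader has still to make. A reader serving on both committees could sign the BS baseline, see which lesions regressed at 6 months, and then read the PET/CT baseline, or do so in the reverse order.

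Regression under treatment is what defines the reference standard, so the second baseline read would be made with part of the reference result in hand. A lesion known to have regressed is more likely to be called malignant, and one known to have persisted is more likely to be called benign. Both shifts favour the modality read later.

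The primary objective is a patient-level comparison of BS with PET/CT. The sample size rests on false positive fractions, and the stated test is McNemar's. A bias that follows reading order acts on one member of the pair only, so pairing does not cancel it. It could create a difference between modalities or hide one.

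**Working it through.** **Step 1: does the text permit it?** No stated figure is at issue, so this is a check of the rules against each other.

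1. *Trigger.* Follow-up images open when the baseline scan for a patient has been read and signed (Follow up images). The text says scan, in the singular, for a patient. It does not require the other modalities' baseline scans to have been read. Committees are described by modality, and the three modalities are brought together only in equivocal or inconsistent cases. The natural reading is therefore a trigger within one modality, although the sentence does not name one.
2. *Overlap.* A reader may sit on more than one committee (Image analysis).
3. *Order.* No order across modalities, interval or separate session is stated.
4. *Population.* Follow-up scans are done only in patients with a satisfactory response (Study design), so the exposure is confined to them.
5. *Joint session.* If inconsistent means disagreement between modalities, as the word is used under Final diagnosis, each modality has already been read and the joint session cannot inform a later baseline read. An equivocal case could reach the joint session earlier, and the text does not exclude that.

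The sequence needs three conditions together: the same reader, one modality's follow-up opened before another modality's baseline read, and a patient with follow-up scans. The text allows all three and excludes none.

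**Step 2: what could it do to the comparison?** The article gives neither the specificities nor the degree of contamination, so this is an illustration under assumptions.

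Inputs from the article: 114 evaluable patients, 50 % prevalence (stated as prevalence on BS), alpha 5 %, McNemar test. Metastasis-free patients: 114 × 0.50 = 57.

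Assumptions: both modalities have the same true false positive fraction *f*; reads are independent; the test is two-sided; the same modality is read later in every patient; and outcome knowledge removes a share *c* of that modality's false positives. The discordant probabilities are then:

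- positive on the earlier-read modality only: f × [1 − f(1 − c)]
- positive on the later-read modality only: f(1 − c) × (1 − f)

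For f = 0.30 and c = 0.25: 0.30 × 0.775 = 0.2325 and 0.225 × 0.70 = 0.1575. Among 57 patients that is about 13.3 against 9.0 discordant patients, where without contamination the two would be equal.

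Simulated rate of false significance (40,000 runs), asymptotic McNemar with the exact version in brackets:

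| f | c = 0 | c = 10 % | c = 25 % | c = 50 % |
|---|---|---|---|---|
| 0.20 | 5.1 % (3.0 %) | 5.9 % (3.5 %) | 10.7 % (7.1 %) | 30.8 % (23.2 %) |
| 0.30 | 5.5 % (3.1 %) | 6.9 % (3.9 %) | 15.3 % (10.1 %) | 49.3 % (39.3 %) |
| 0.40 | 5.5 % (3.1 %) | 7.7 % (4.7 %) | 20.7 % (14.2 %) | 65.7 % (55.9 %) |

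The bias can also hide a difference. With assumed true fractions of 0.30 for BS and 0.10 for PET/CT, reading BS later and removing a quarter of its false positives gives 0.30 × 0.75 = 0.225. The difference falls from 0.20 to 0.125.

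**Step 3: how many discordant patients carry the test?** At the same assumed 0.30 and 0.10, independence gives 57 × (0.30 × 0.90 + 0.10 × 0.70) = 57 × 0.34 = 19.4. Minimal discordance gives 57 × 0.20 = 11.4. The range is wide because the article fixes neither the fractions nor their correlation.

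**The case against.** The strongest reply is that this is a condensed article. It refers to a reader manual and a standardised protocol for image analysis, and session order or reader allocation may be set there. That deserves weight: the absence of a washout or a randomised order in the article is not a fault in itself. However, the items the article hands on are named. Image analysis defers the measurement scales and the handling of multiple lesions; Final diagnosis defers inconsistent responses between modalities. Reading order is not among them. The article states its own trigger for opening follow-up images, and the Discussion says the reading conditions are fully described. What remains is a stated rule that does not protect the other modalities' baseline reads.

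Four stronger readings are tempting and not supported:

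- *That later baseline reads will be made by someone who knows the outcome.* Overlap is optional, no order is fixed, and nothing says follow-up is opened immediately after the baseline read.
- *That the procedure contradicts the blinding claim.* Blinded is undefined in the abstract, and signing the baseline CRF before follow-up is consistent with a baseline read blind to outcome for that scan. The claim is unsecured across modalities, not contradicted.
- *That equivocal cases supply most of the discordant pairs.* This is plausible, but the article offers nothing to show it.
- *That the simulated rates estimate the bias in this trial.* They rest on an assumed *c*, applied to every patient in one fixed order. A mixed order, partial overlap, or patients without follow-up would dilute it. The 57 also borrows a prevalence on BS, not by the reference standard.

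**Conclusion.** The point holds in conditional form. For patients with follow-up scans, the rules on opening follow-up images and on committee membership together allow a baseline BS or PET/CT call by a reader who has already seen regression on another modality, and no stated safeguard prevents it. The direction is clear: the modality read later is favoured, and the paired comparison is biased accordingly.

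The size cannot be computed from the document, because the extent of overlap, the reading order and the effect of outcome knowledge are all unknown. Under the illustrative assumptions, contamination of 10 % does little (6–8 % false significance over fractions of 0.20 to 0.40, asymptotic test), while 25 % gives 11–21 % (exact test 7–14 %). The matter should be settled before reading starts, because reads made with outcome knowledge cannot be corrected in the analysis.

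**What to change.** 1. **Change the trigger under Follow up images.** The consensus baseline reads of BS, SPECT/CT and PET/CT, with signed CRFs, are all locked for a patient before any follow-up image or joint multi-modality session for that patient is opened. A lock per patient is enough for this mechanism; a lock on the whole cohort is not needed.
2. **Separate the sessions.** A reader on more than one committee reads each modality's baseline scans in a separate session, without the other modality's result.
3. **Define the blinding.** State that baseline readers are blinded to the other modalities and to follow-up, alongside the clinical information they do receive.

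*Optional:* the readers who made the baseline call also make the side-by-side classification. Where the existing pool allows, a reader should preferably not classify at follow-up the modality they read at baseline for that patient. The size of the pool is not given, so this might need extra readers and should not be a condition.

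*Cost:* items 1 to 3 need no additional scans or patients. They require scheduling of reads and an edit to the reader manual, and the follow-up classification becomes available slightly later.

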#### Final diagnosis

A map of lesions identified by all imaging modalities will be drawn. Some lesions may be observed on all imaging modalities, while other lesions may be observed only in one or two modalities. The lesions will be analysed per modality and combined and classified as: 1) **True positive:** A lesion that was defined as M+ on the baseline image and that responded to ADT on on any follow-up images, 2) **False positive:** A lesion that was defined as M+ on the baseline image but did not respond to ADT in any of the imaging modalities, 3) **False negative:** A lesion that was not identified on one imaging modality at baseline, but turned out to eventually be classified as M+ on other imaging modalities, e.g. a lesion that was not detected by BS but detected and classified as true positive on ^18^F-fluoride PET/CT will be classified as false negative on BS, see Fig. 1, and 4) **True negative:** A lesion that was not identified on one imaging modality at baseline, and was eventually classified as M- on other imaging modalities as well. Patients with at least one lesion characterised as malignant by any imaging modality will be classified as malignant on an individual patient basis. How to handle inconsistent responses between imaging modalities will be specified in the statistical analysis plan. For lesions-based analysis, final diagnosis is determined by the same criteria as for the patient-based analysis, as described above.

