## Methods/Design

### Study objectives

The primary objective of this study is to assess the diagnostic accuracy of ^18^F-fluoride PET/CT for detection of bone metastases compared with BS in newly diagnosed, high risk, untreated prostate cancer patients on an individual patient basis.

Secondary objectives are: 1) to assess the diagnostic properties of SPECT/CT in comparison with BS and ^18^F-fluoride PET/CT, 2) to evaluate the diagnostic properties of all imaging modalities on the basis of individual lesions, 3) to investigate the inter- and intra-observer variation of SPECT/CT and ^18^F-fluoride PET/CT, and 4) to investigate the predictive role of bone tumour load as measured by ^18^F-fluoride PET/CT as a predictor of time to loss of hormone sensitivity.

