### Data analysis

A detailed statistical analysis plan, including considerations for secondary endpoints, will be issued prior to analysis. Data analysis will primarily focus on the diagnostic accuracy of BS and ^18^F-fluoride PET/CT. Sensitivity, specificity, positive and negative predictive values, and likelihood ratios will be calculated for each imaging modality with 95 % confidence intervals and will be compared using the McNemar test, with *P* < 0.05 being statistically significant.

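### Lesion-level true negatives are drawn only from lesions that another modality shows, so lesion specificity depends on the set of tests in the study as well as on each modality's own false calls

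*Protocol article*

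**What the plan says.** Secondary objective 2 (Study objectives) is "to evaluate the diagnostic properties of all imaging modalities on the basis of individual lesions". The Final diagnosis section sets up the lesion analysis. First, "A map of lesions identified by all imaging modalities will be drawn", so the pool of lesions is the union of what the study modalities display. Four cells are then defined. A true negative is "A lesion that was not identified on one imaging modality at baseline, and was eventually classified as M- on other imaging modalities as well". A false positive is "A lesion that was defined as M+ on the baseline image but did not respond to ADT in any of the imaging modalities". The false negative cell also turns on a lesion not being identified, and its worked example speaks of "a lesion that was not detected by BS but detected and classified as true positive on" PET/CT. In this section, therefore, not identified means not detected.

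The Image analysis section has every lesion (or a representative sample where there are many) "classified independently by each reader for malignancy using a dichotomous scale". Lesions that a modality shows and its readers call benign will therefore exist in the data.

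The same section on final diagnosis adds: "For lesions-based analysis, final diagnosis is determined by the same criteria as for the patient-based analysis, as described above". Under Data analysis, "Sensitivity, specificity, positive and negative predictive values, and likelihood ratios will be calculated for each imaging modality with 95 % confidence intervals", with comparison by the McNemar test.

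**The concern.** Bone without uptake has no countable number of negative lesions, so a lesion-level specificity needs a denominator from somewhere. The definition takes it from the other tests: BS can be credited with a true negative only where PET/CT or SPECT/CT shows a benign spot that BS does not.

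Two consequences follow. Adding or dropping a test changes a modality's lesion specificity with no change in how that modality is read. And a modality that displays a benign lesion and reads it correctly gets no credit, while a modality that does not display it does. PET/CT is described in the Background as having higher bone uptake and spatial resolution than BS. If it therefore shows more benign lesions, which is an assumption here, the rule would work against it even when its readers make fewer false calls. At stake is the direction and size of the BS v PET/CT specificity comparison for secondary objective 2.

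**Working it through.** The article states no lesion counts, no lesion-level specificity and no lesion-level power, so there is no figure to reproduce. The sample size of 114 is calculated per patient and does not bear on this point. All counts below are assumptions for illustration.

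**Illustration A: change only the set of tests.** Take 80 finally benign lesions:

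| Lesions | BS | PET/CT | SPECT/CT |
|---|---|---|---|
| 4 | M+ | M+ | M+ |
| 6 | M+ | benign | benign |
| 4 | not seen | M+ | not seen |
| 18 | benign | benign | benign |
| 26 | not seen | benign | not seen |
| 2 | benign | not seen | benign |
| 20 | not seen | not seen | benign |

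False positives (FP): BS 4 + 6 = 10; PET/CT 4 + 4 = 8. These are held fixed throughout. Specificity = TN/(TN + FP), where TN is the number of true negatives.

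*Literal rule* (TN = not seen by the modality, shown by another test in the study, finally benign):

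| Tests in study | BS | PET/CT | BS minus PET/CT |
|---|---|---|---|
| BS alone | 0/10 = 0% | – | – |
| BS + SPECT/CT | 20/30 = 66.7% | – | – |
| BS + PET/CT | (4 + 26)/40 = 75.0% | 2/10 = 20.0% | +55.0 points |
| All three | (4 + 26 + 20)/60 = 83.3% | (2 + 20)/30 = 73.3% | +10.0 points |

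BS specificity runs from 0% to 83.3% with its 10 false calls unchanged. Both comparisons favour BS, which makes more false calls. The paired comparison is distorted too. The 6 lesions that BS calls malignant and PET/CT correctly calls benign have no PET/CT cell, so they drop out. The 4 that only PET/CT calls malignant stay in. The discordant lesions become 0 v 4 instead of 6 v 4.

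*Amended rule* (seen and called benign also counts as TN): both modalities now share one benign pool.

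| Tests in study | BS | PET/CT | PET/CT minus BS |
|---|---|---|---|
| BS + PET/CT (pool 60) | 50/60 = 83.3% | 52/60 = 86.7% | 3.3 points |
| All three (pool 80) | 70/80 = 87.5% | 72/80 = 90.0% | 2.5 points |

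The direction now follows the false calls, and the discordant lesions are 6 v 4 in both rows. The level and the difference still move with the pool, because the difference equals (FP for BS minus FP for PET/CT)/pool = 2/60 or 2/80.

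**Illustration B: change only the size of the shared pool, amended rule.** Assume 100 men, with 30 BS and 10 PET/CT false positive lesions that do not overlap.

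- 100 other benign lesions, correctly read: pool 140; 110/140 = 78.6% v 130/140 = 92.9%; difference 14.3 points.
- 300 such lesions: pool 340; 310/340 = 91.2% v 330/340 = 97.1%; difference 5.9 points.

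In both cases false positives per man are 0.30 v 0.10, the ratio of false positive fractions is 30/10 = 3.0, and the McNemar statistic (ignoring clustering) is (30 − 10)²/40 = 10.

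**Own false calls.** With TN fixed at 30, raising FP from 5 to 10 to 20 gives 30/35 = 85.7%, 30/40 = 75.0% and 30/50 = 60.0%. The modality's own false calls clearly still matter.

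**The case against.** A reader might infer that lesion specificity reflects the other tests *instead of* the modality's own false calls. The definitions do not support that: false positives stay in TN/(TN + FP), and the last calculation moves specificity by about 26 points through them alone.

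The best defence is that a sensible analyst would count seen-and-called-benign lesions as true negatives. On a shared pool the direction, the McNemar discordant counts and the ratio of false positive fractions then come from the modalities' own false calls, and only the level and absolute difference are rescaled. This is correct, and the reversed direction in Illustration A arises only under the literal rule. But the literal rule is what the article states.

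It may also be said that the summary measure for a secondary analysis belongs in the statistical analysis plan (SAP). The article does defer measurement scales, multiple lesions, inconsistent responses and secondary endpoints to later documents, and it does not say outright that predictive values and likelihood ratios will be reported per lesion. That answers the choice of measure. It does not answer the true negative definition, which is fixed in the text.

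Finally, the alternatives are not wholly free of the other tests. Lesion sensitivity rests on false negatives found by other modalities. A false positive is a lesion that responds on none of them, so an added test that shows response would relabel it. With fixed regions, the number of regions chosen scales specificity. All of this stands and shapes the fix.

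**Conclusion.** The point holds for the secondary lesion-based analysis. As written, the true negative cell is filled only by what other tests display and leaves out benign lesions that a modality sees and reads correctly. The resulting specificity can favour the modality that shows fewer benign lesions: by 55 points with two tests and 10 points with three in Illustration A, against the false-call counts. With the cell completed, the direction is sound, but the level and absolute difference still scale with the pool (14.3 v 5.9 points in Illustration B). The sizes rest on assumed counts and on holding the false positive labels fixed as tests are added; the true sizes cannot be known from the article.

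Two wider inferences are not supported. The patient-level primary analysis and the sample size of 114 (140 recruited) are unaffected, because patients are countable units and do not depend on the lesion true negative cell. Nor can it be said from this document that the lesion results could not be compared with other studies, since how those studies counted lesions is not shown.

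**What to change.** For the lesion-based analysis only:

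1. Amend the true negative definition to include finally benign lesions that the modality saw and called benign.
2. Make false positive lesions per patient, for each modality, the lesion-level measure of false calls, with the paired difference and a patient-clustered 95% CI. Alternatively, compute specificity on skeletal regions listed in the reader manual before reading starts, so that the denominator is the same whatever tests are used.
3. State that lesion sensitivity and the false positive label remain relative to the combined reference formed by the study modalities.

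The cost is wording in the definition, the SAP and, for the regional option, the reader manual. The counts come from the planned lesion map and the baseline calls, so no new data are needed. Where only a representative sample of a patient's lesions is classified, the SAP should say how that patient's count is formed. The article reports the trial as recruiting and the SAP as due before analysis, so there is time. The downside of reporting false positives per patient is that there is no single lesion specificity to set beside earlier papers.
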